**4.** **INCLUSION CRITERIA**

1. Histologically or cytologically confirmed diagnosis of cancer (including epithelial carcinoma, sarcoma, and melanoma)
2. Age 18 years or older
3. Life expectancy > 3 months
4. Patients with AJCC (6th edition, 2002) stage IV cancer with distant metastases and without pleural or pericardial effusion at diagnosis and before start of study
   1. Patients with pleural effusion that is transudative, cytologically negative,

and non-bloody are eligible

- 1. If a pleural effusion is too small for diagnostic thoracentesis, the patient will be eligible.

1. Patients with 1-5 sites of maximum tumor dimension (for each individual site) of ≤ 10 cm or < 500 cc volume and amenable to radiation therapy as seen on standard imaging (CT, MRI, bone scan, PET/CT)
2. Unidimensionally measurable disease (based on RECIST) is desirable but not strictly required.
3. Brain metastases must have been treated prior to enrollment on study, preferably with stereotactic radiosurgery or surgery.
4. Eastern Cooperative Oncology Group (ECOG) performance status ≤ 2 (Karnofsky ≥ 60%)
5. No prior radiation therapy to currently involved tumor sites
6. Room air saturation (SaO2) > 90%
7. Patients must have normal organ and marrow function as defined below:

Hemoglobin > 9.0 g/dl

Absolute neutrophil count (ANC)  1,500/l

Platelets  100,000/l

Total bilirubin within institutional limits

Albumin > 2.9 g/dl

Alkaline phosphatase < 2.5x upper limit of normal

AST and ALT <2.5 x upper limit of normal

1. Informed consent must be obtained from all patients prior to beginning therapy. Patients should have the ability to understand and the willingness to sign a written informed consent document.
2. Inclusion of Women and Minorities: Both men and women of all ethnic groups are eligible for this trial. The proposed study population is in the table below:

Table 2:

|  | White, not of Hispanic origin | Black, not of Hispanic origin | Hispanic | Asian or Pacific Islander | Unknown | Total |
| --- | --- | --- | --- | --- | --- | --- |
| Male | 24 | 4 | 6 | 2 | 0 | 36 |
| Female | 20 | 3 | 5 | 1 | 0 | 29 |
| Total | 44 | 7 | 11 | 3 | 0 | 65 |

1. Radiation therapy requirements: Patient must have a completed treatment plan approved by the protocol review team ([name] or [name] AND [name] or [name])

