**11. ADDITIONAL INTERVENTIONS – CHEMOTHERAPY, SURGERY AND/OR ADDITIONAL RADIATION**

11.1 Interventions prior to protocol therapy: If chemotherapy, surgery and/or radiation are recommended by the treating physicians based on the patient’s clinical needs, they may be performed two weeks before or after days 1-28 of protocol therapy.

For instance, a patient with a history of breast cancer status post mastectomy (three years ago) and adjuvant chemotherapy now presents with a solitary brain metastasis, a single lung lesion and two bone lesions. The brain metastasis and lung lesion are both amenable to resection. Subsequently, the patient receives whole brain radiation and taxane based chemotherapy. After chemotherapy, CT of the chest abdomen and pelvis and MRI of the brain reveal no evidence of metastatic disease but bone scan demonstrates residual uptake in the two bone lesions. Two weeks after completion of chemotherapy, the patient is eligible for protocol therapy. The patient will receive Sutent on days 1-28 and extracranial stereotactic radiation on days 8-12 and 15-19 as per protocol. Two weeks after protocol therapy (day 43), the patient may receive additional chemotherapy. After completion of all planned chemotherapy, the patient will start maintenance Sutent. Therefore, all of the chemotherapy, surgery and whole brain radiation are allowed by protocol but are not considered “on protocol therapy”. While all toxicities of these interventions will be documented and recorded, any toxicity resulting from non-protocol therapy will not count as dose-limiting toxicity.

11.2 If patients have documented progression during additional chemotherapy and/or maintenance Sutent, the patient will be taken off protocol. At that time, any necessary intervention (chemotherapy, surgery and/or radiation will be allowed).

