**13. MEASUREMENT OF EFFECT**

- Response and progression will be evaluated in this study using the new international criteria proposed by the RECIST Committee. (38) Changes in only the largest diameter (unidimensional measurement) of the tumor lesions are used in the RECIST criteria.
- All lesions (except lesions seen on bone scan alone) are considered to be target lesions and are measurable. They are defined as being accurately measured in one dimension (longest diameter to be recorded). All tumors must be recorded in millimeters (or decimal fractions of centimeters) using a ruler or caliper.
- Lesions seen on bone scan only are not measurable and therefore are evaluated separately
- All baseline evaluation should be performed as closely as possible to beginning of the treatment and never more than 4 weeks before the beginning of treatment.
- The same method of assessment and the same technique should be used to characterize each identified and reported lesion at baseline and during follow-up.
- First assessment should be performed 4-6 weeks after completion of radiation therapy.
- Response Criteria for all lesions (except lesions seen only on bone scan):
  - Complete response (CR): Disappearance of all lesions
  - Partial response (PR): At least 30% decrease in the sum of the longest diameter (LD) of all lesions, taking as a reference the baseline sum LD
  - Progressive disease (PD): At least a 20% increase in the sum of the LD of the target lesions, taking as a reference the smallest sum LD recorded since the treatment started or the appearance of one or more new lesions
  - Stable disease (SD): Neither sufficient shrinkage to qualify for PR or sufficient increase to qualify for PD, taking as reference the smallest LD since the treatment started.
- Response Criteria for lesions seen only on bone scan:
  - Complete response (CR): Disappearance of lesion.
  - Stable disease (SD): Persistence of lesion on bone scan.
- Evaluation of best overall response:
  - The best overall response is the best response recorded from the start of the treatment until disease progression/recurrence (taking as reference for progressive disease the smallest measurements recorded since the treatment started). The patient’s best response assignment will depend on the achievement of both measurement and confirmation criteria:

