**Table 3**

| **All Measurable Lesions** | **Lesions on bone scan only** | **New Lesions** | **Overall Response** |
| --- | --- | --- | --- |
| CR | CR | No | CR |
| CR | SD | No | PR |
| PR | SD | No | PR |
| SD | Any | No | SD |
| PD | Any | Yes or No | PD |
| Any | Any | Yes | PD |

CR = complete response; PD = progressive disease; PR = partial response; SD = stable disease

- Note:
  - Patients with a global deterioration of health status requiring discontinuation of treatment without objective evidence of disease progression at that time should be classified as having “symptomatic deterioration.” Every effort should be made to document the objective progression, even after discontinuation of treatment.
  - In some circumstances, it may be difficult to distinguish residual disease from normal tissue. When the evaluation of complete response depends on this determination, it is recommended that the residual lesion be investigated (fine needle aspirate/biopsy) before confirming the complete response status.
- Confirmatory Measurement/Duration of Response
  - Confirmation
    - To be assigned a status of PR or CR, changes in tumor measurements must be confirmed by repeat assessments that should be performed at least 16 weeks after the criteria for response are first met.
  - Duration of Overall Response
    - The duration of overall response is measured from the time measurement criteria are met for CR or PR (whichever is first recorded) until the first date that recurrent or progressive disease is objectively documented (taking as reference for progressive disease the smallest measurements recorded since the treatment started).
    - The duration of overall CR is measured from the time measurement criteria are first met for CR until the first date that recurrent disease is objectively documented
  - Duration of Stable Disease
    - Stable disease is measured from the start of the treatment until the criteria for progression are met, taking as reference the smallest measurements recorded since the treatment started.
- Progression-Free and Overall Survival
  - Progression-free (time to progression): From the date of registration to the date of progressive disease or death
  - Overall survival time: From the date of registration to the date of death or date of last patient contact if censored

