  - All patients who have met the eligibility criteria will be included in the main analysis of the response rate. Patients in response categories 4 – 8 will be considered as failing to respond to treatment (disease progression).
  - All individual lesions will also be recorded as CR, PR, SD, or PD.
  - Overall survival is the time from the date of first study treatment until death from any cause.

Overall survival and progression-free survival (PFS) will be calculated using the Kaplan-Meier (1958) estimator.(40) Median survival times and their associated 90% confidence intervals will be derived using the method described in Brookmeyer and Crowley (1982).(41)

The percentage of patients with complete responses and the percentage with complete or partial responses will be calculated and confidence intervals derived. The pattern of failures (local or distant) will be summarized. Adverse effects will also be tabulated by type and level of severity. Potential prognostic variables, such as number of lesion sites at baseline, will be examined by fitting Cox (1972) regression models for progression-free and overall survival times.(42) Given the sample size, only univariate analysis will be performed.

- Accrual Rate and Study Duration
  - The estimated accrual will depend on toxicity encountered, but we anticipate enrolling 50-65 patients.
  - We anticipate enrolling 1-3 patients per month.

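### Section 13 gives lesions seen only on bone scan no progression criterion, so their worsening delays or misses a PFS event and can bias PFS only upward

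*Protocol*

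**What the plan says.** Section 13 splits lesions into two groups. Everything except lesions seen on bone scan alone is a measurable target lesion. For the rest, "Lesions seen on bone scan only are not measurable and therefore are evaluated separately". That separate evaluation has two categories: "Complete response (CR): Disappearance of lesion" and "Stable disease (SD): Persistence of lesion on bone scan".

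Progressive disease requires "At least a 20% increase in the sum of the LD of the target lesions", measured from the smallest sum recorded, or the appearance of a new lesion. Table 3 follows the same logic: overall PD comes from PD in measurable lesions or from a new lesion. Stable measurable disease with any bone-scan status and no new lesion is rated SD overall.

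The progression-free interval, defined after Table 3, runs "From the date of registration to the date of progressive disease or death". PFS is a phase II primary endpoint (Section 1).

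Patients without measurable disease may enter: "Unidimensionally measurable disease (based on RECIST) is desirable but not strictly required" (Section 4). The worked example in Section 11.1 describes an eligible patient whose body CT and brain MRI are clear while "bone scan demonstrates residual uptake in the two bone lesions".

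Section 16 has each individual lesion recorded as CR, PR, SD or PD, and adds that "The pattern of failures (local or distant) will be summarized".

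**The concern.** The purpose of the radiation is to control the treated sites. For one class of treated site, the written rule has no way to record that control was lost. A patient like the one in Section 11.1 can have both irradiated bone lesions worsen and still be scored SD, or fall outside Table 3 altogether, until something else happens.

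The error has one direction. Recorded PFS is equal to or later than PFS counted with local bone progression included, and never earlier. The trial is single-arm and is judged against an assumed historical median of 6.4 months (Section 16), so no concurrent control arm shares the leniency.

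Sections 13 and 16 also disagree. One expects a PD label to be available for every lesion, and the other supplies no criterion for it in this class. The local-versus-distant failure summary would then rest on undefined calls for these lesions.

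**Working it through.** **1. The rules side by side**

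| Situation, no new lesion | Result under Section 13 and Table 3 |
| --- | --- |
| Measurable disease stable, bone-scan-only lesion worse | SD |
| Measurable disease in CR, bone-scan-only lesion worse but still scored as persisting (SD) | PR |
| No measurable lesion, bone-scan-only lesion worse | Lesion SD; no row in Table 3 |
| Measurable disease PD | PD |

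In the first three rows no PFS event is recorded, whatever happens in the bone lesion.

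**2. The plan's own figures**

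Inputs from Section 16: n = 38, median time to progression 6.4 months, SD 3.2 months, a 25% increase (0.25 × 6.4 = 1.6 months), α = 0.05.

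- One-sample normal test, two-sided: Φ(√38 × 1.6/3.2 − 1.96) = Φ(3.08 − 1.96) = 0.869. This matches the stated 87%.
- 2-year PFS, 5% versus 15%: the normal approximation gives 0.702. The exact rule of at least 5 of 38 has α = 0.040 and power 0.693. Both match the stated 70%.

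Neither figure is in dispute. They are reproduced so that the bias can be put on the same scale.

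**3. Assumptions for size**

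The documents give neither the share of patients with bone-scan-only disease nor the delay.

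- Share with bone-scan-only disease: 10-40% (assumed).
- Of these, first failure at a treated site without a new lesion: 10-20% (assumed; Section 2b cites local control above 80% for spine, lung and liver).
- Affected share s: 0.10 × 0.10 = 1% to 0.40 × 0.20 = 8%, that is 38 × 0.01 = 0.4 to 38 × 0.08 = 3.0 patients.
- Delay D until another event is recorded: 3 to 6 months (assumed; equal to the scan intervals in Section 7.4).

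**4. Effect on time to progression**

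Shift in the mean = s × D. Upper-tail error with no true benefit, SD held at 3.2 = Φ(√38 × sD/3.2 − 1.96), nominal 0.025.

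| s | D (months) | Shift (months) | Share of 1.6 | Upper-tail error |
| --- | --- | --- | --- | --- |
| 1% | 3 | 0.03 | 2% | 0.029 |
| 4% | 6 | 0.24 | 15% | 0.067 |
| 8% | 3 | 0.24 | 15% | 0.067 |
| 8% | 6 | 0.48 | 30% | 0.15 |

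The delay also adds variance, s(1 − s)D². At the last row the variance becomes 3.2² + 0.08 × 0.92 × 36 = 12.89. The error is then 0.18 if the test still uses SD 3.2, and 0.13 if it uses the SD in the data. The order of size is unchanged.

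**5. Effect on the 2-year comparison**

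A missed local failure counts as a 2-year success only if the patient is otherwise free of events at 2 years. Taking the plan's own 5% and 15% as the assumed chance of that:

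- Patients wrongly counted: 38 × 0.01 × 0.05 = 0.02 to 38 × 0.08 × 0.15 = 0.46.
- Largest null rate: 0.05 + 0.08 × 0.15 = 0.062, for which P(at least 5 of 38) = 0.084 instead of 0.040.
- With s = 8% and the 5% figure, the null rate is 0.054 and the error 0.052.

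**The case against.** The strongest reply is that the affected group is narrow and the failure is seldom lost.

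- **Narrow group.** The class covers lesions seen on bone scan alone. Section 7.1 lists plain film, CT or MRI of bone-scan abnormalities before therapy, and a lesion visible there is arguably no longer in the class. Whole-body PET/CT may replace CT plus bone scan, which may shrink the group further. The example in Section 11.1 shows that such a patient is possible, not that such patients are common.
- **Delay rather than loss.** A later new lesion, measurable progression or death still ends PFS. A lesion that becomes visible on follow-up CT or MRI might be counted. However, Section 13 has no reclassification rule, and Section 7.4 asks for that imaging at follow-up only if clinically indicated.

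Both points stand as limits on size. Neither supplies the missing criterion or changes the direction of the error.

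A reader might infer three stronger things that the documents do not support:

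- *Local failure in these lesions can never become a PFS event.* This ignores the later routes to an event just listed.
- *The rule removes these failures from the local/distant summary.* Section 16 permits a PD label for every lesion and does not say that the summary is derived from Table 3. What the text shows is a conflict between sections, not a built-in exclusion.
- *One to three misclassified patients could decide the 2-year result, which turns on about 5 of 38.* This treats every missed local failure as a 2-year success. Most such patients would have another event before then.

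**Conclusion.** The point holds as a defect in the definition of a primary endpoint. Section 13 and Table 3, applied as written, score a worsening bone-scan-only lesion as stable and leave some eligible patients unclassifiable unless a new lesion appears. Section 16 contradicts Section 13 on whether such a lesion can be PD. These conclusions come from the text alone and need no assumption.

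The bias in PFS is upward or zero. Its size rests on assumed values of s and D. Over the range used it runs from negligible to about 30% of the target improvement, with limited effect on the 2-year test. Larger shares or longer delays would give more, but nothing in the protocol supports a particular value. The correction is worth making because the rule is wrong and cheap to repair, not because the trial's conclusion is shown to depend on it.

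**What to change.** In Section 13, add a PD category for lesions seen only on bone scan, for example unequivocal worsening on bone scan, or structural progression on the plain film, CT or MRI that Section 7.4 already allows. State how a lesion is handled once it becomes visible on other imaging.

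In Table 3, let bone-scan PD give overall PD, and add rows for patients with no measurable lesion and bone status CR, SD or PD. The table also lacks a row for measurable PR with bone CR, which can be added at the same time.

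In Section 16, refer to the same criterion for lesion-level recording, and count this progression as local failure in the failure summary.

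The cost is wording and a slightly less favourable PFS estimate. No new scheduled scans are needed, and the 38 patients and stated power are unaffected. Sections 6 and 11.2 tie progression to leaving treatment or protocol, so the investigators should check those sections against the new category. This point takes no position on how they should read.

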**Table 3**

| **All Measurable Lesions** | **Lesions on bone scan only** | **New Lesions** | **Overall Response** |
| --- | --- | --- | --- |
| CR | CR | No | CR |
| CR | SD | No | PR |
| PR | SD | No | PR |
| SD | Any | No | SD |
| PD | Any | Yes or No | PD |
| Any | Any | Yes | PD |

CR = complete response; PD = progressive disease; PR = partial response; SD = stable disease

- Note:
  - Patients with a global deterioration of health status requiring discontinuation of treatment without objective evidence of disease progression at that time should be classified as having “symptomatic deterioration.” Every effort should be made to document the objective progression, even after discontinuation of treatment.
  - In some circumstances, it may be difficult to distinguish residual disease from normal tissue. When the evaluation of complete response depends on this determination, it is recommended that the residual lesion be investigated (fine needle aspirate/biopsy) before confirming the complete response status.
- Confirmatory Measurement/Duration of Response
  - Confirmation
    - To be assigned a status of PR or CR, changes in tumor measurements must be confirmed by repeat assessments that should be performed at least 16 weeks after the criteria for response are first met.
  - Duration of Overall Response
    - The duration of overall response is measured from the time measurement criteria are met for CR or PR (whichever is first recorded) until the first date that recurrent or progressive disease is objectively documented (taking as reference for progressive disease the smallest measurements recorded since the treatment started).
    - The duration of overall CR is measured from the time measurement criteria are first met for CR until the first date that recurrent disease is objectively documented
  - Duration of Stable Disease
    - Stable disease is measured from the start of the treatment until the criteria for progression are met, taking as reference the smallest measurements recorded since the treatment started.
- Progression-Free and Overall Survival
  - Progression-free (time to progression): From the date of registration to the date of progressive disease or death
  - Overall survival time: From the date of registration to the date of death or date of last patient contact if censored

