7.3 Supportive Care

- Antiemetics will be ordered at the discretion of the attending physician.
- Mucositis/esophagitis may be ameliorated with sulcrafate or GI cocktail (e.g. Tylenol #3 suspension, bendaryl elixir, Maalox, viscous lidocaine).
- Intravenous hydration is recommended in patients with inadequate oral intake.
- Treatment-related diarrhea will be managed with high-dose loperamide. The recommended dose of loperamide is 4 mg initially (two capsules) then 2 mg after each loose stool, not to exceed 16 mg daily.

7.4 Follow-up checklist: Follow-up visits are to be done every 2 weeks for first 2 months;
 then every 3 months for 1 years; then every 6 months indefinitely

- History and Physical
- Documentation of current medications
- Adverse effect assessment
- CT scan of chest, abdomen, and pelvis (initially 4-6 weeks following completion of radiation therapy to assess response; then every 3 months for first year then every 6 months indefinitely)
- Bone scan (initially 4-6 weeks following completion of radiation therapy to assess response; then every 3 months for first year then every 6 months indefinitely). The bone scan is optional if the patient did not have any evidence of disease on the bone scan upon enrollment into the trial.
- Whole body 18-FDG PET/CT initially 3 months following completion of radiation therapy and every 3 months for the first year and every 6 months thereafter is an acceptable alternative to CT of chest, abdomen and pelvis and bone scan
- Plain X-ray and/or CT and/or MRI of bone abnormality seen on bone scan (if clinically indicated)
- MRI brain if clinically indicated
- Hematology: CBC (hemoglobin, white blood cell count, platelets) with differential
- Biochemistry: Comprehensive metabolic profile (glucose, sodium, potassium, chloride, carbon dioxide, BUN, creatinine, calcium, total bilirubin, alkaline phosphatase, AST, ALT)- (every 3 months for first 2 years then every 6 months indefinitely)
- Tumor markers, if elevated prior to treatment, are recommended
- 18-FDG PET scan every 6 months (optional).

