**16. STATISTICAL CONSIDERATIONS**

- Phase I: The primary objectives are to determine the maximum tolerated dose (MTD) and dose limiting toxicity (DLT) of extracranial stereotactic radiation therapy in combination with Sutent when given to all sites of involved disease in patients with metastatic cancer.
- For dose escalation purposes, the major endpoint will be dose-limiting toxicity occurring within 30 days after the start of radiation therapy.
- Dose limiting toxicity is defined as follows: Grade 3-5 non-hematological toxicities (excluding nausea, vomiting, and alopecia) and Grade 4-5 hematological toxicities.
  - Esophagitis and mucositis are very common side effects with radiation therapy and grade 3 side effects can be seen after palliative courses of radiotherapy. Therefore, grade 3 mucositis or esophagitis lasting ≤ 7 days will not be considered a DLT. If the grade 3 mucositis or esophagitis lasts > 7 days, it will then be considered a DLT.
- The MTD for a specific area will be exceeded if 2 or more patients out of 6 (or a third or more) with disease at that site experience DLT at that dose. The dose immediately below will be recommended for further study.
- Phase II: *(Includes 3 to 6 patients from Phase I MTD):* The median progression free survival with optimal chemotherapy alone for the 4 most common tumor types (lung, breast, prostate and colorectal) ranges from 2.2 to 10.6 months, depending on primary tumor site and degree of pretreatment. Therefore, we will assume a median time to progression of 6.4 months (standard deviation 3.2 months) with chemotherapy alone. With 38 patients, this study has 87% power (α=0.05) to detect a 25% increase in time to progression. Also the 2 year freedom from progression is <5% with chemotherapy therapy and this study has 70% power (α=0.05) to demonstrate a 10% absolute increase in 2 year progression-free survival.
  - All patients included in the study will be assessed for response to treatment, even if there are major protocol treatment deviations or if they are ineligible (intent-to-treat population). Criteria described in Section 10 will be used to assign each patient to one of the following response categories: 1) complete response, 2) partial response, 3) stable disease, 4) progressive disease, 5) early death from malignant disease, 6) early death from toxicity, 7) early death because of other cause, or 8) unknown (not assessable, insufficient data).

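### The 16-week confirmation rule for CR and PR does not fit the 3-monthly scan calendar, so the response rate becomes an unlabelled durable response rate

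*Protocol*

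**What the plan says.** Protocol Section 13 (confirmatory measurement) requires a PR or CR to be confirmed by "repeat assessments that should be performed at least 16 weeks after the criteria for response are first met". The same section makes this binding: "The patient’s best response assignment will depend on the achievement of both measurement and confirmation criteria". It also closes the window: "The best overall response is the best response recorded from the start of the treatment until disease progression/recurrence".

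The scan calendar is fixed elsewhere. Section 13 says "First assessment should be performed 4-6 weeks after completion of radiation therapy". For CT and bone scan, Section 7.4 continues "then every 3 months for first year then every 6 months indefinitely", and footnote 8 of the synopsis schedule table gives the same timing. The alternative in Section 7.4 is also 3-monthly in year 1: "Whole body 18-FDG PET/CT initially 3 months following completion of radiation therapy and every 3 months for the first year".

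No scan near 16 weeks after a first response is scheduled, and no extra confirmatory scan is described. Response rate is a secondary phase II endpoint (Section 1). Section 16 plans the percentages with CR and with CR or PR, with confidence intervals.

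**The concern.** The protocol itself fixes both the minimum confirmation interval and the scan dates, and the two do not match. Sixteen weeks is longer than the 3-month interval, so the scan after a first response in year 1 comes too early to confirm it unless it falls after the switch to 6-monthly scanning. Confirmation normally waits for the scan after that.

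Best response stops accruing at progression. A patient with a response at one scan, the same response at the next and progression at the third therefore cannot be assigned PR or CR. A reader of the final report would see a confirmed response rate and would not know that it required about 5-6 months of sustained response. A longer required interval can only lower the confirmed rate or leave it unchanged. How far it falls depends on how long responses last.

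**Working it through.** **1. The plan's own figures.** The protocol gives no expected response rate and no figure for responses lost to confirmation. Its only related calculations are in Section 16, and both reproduce with two-sided α = 0.05:
- 25% increase in time to progression, n = 38: difference 0.25 × 6.4 = 1.6 months; SE = 3.2/√38 = 0.519; Φ(1.6/0.519 − 1.96) = 86.9% (stated 87%).
- 2-year PFS 5% versus 15%, n = 38: Φ[(0.10 − 1.96·√(0.05·0.95/38)) / √(0.15·0.85/38)] = Φ(0.0307/0.0579) = 70.2% (stated 70%).

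Neither uses the response rate, so the confirmation rule does not touch them.

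**2. The calendar.** 3 months = 13.0 weeks, 6 months = 26.1 weeks, 16 weeks = 3.68 months. The text does not say whether the 3-month visits count from the end of radiation or from the first scan, so both are shown, in weeks after radiation.

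| Counting from | Scan weeks | Year-1 gaps (weeks) |
|---|---|---|
| End of radiation | 4 or 6, 13.0, 26.1, 39.1, 52.2, then 78.3 | 9.0 or 7.0, then 13.0 |
| First scan at 4 | 4, 17.0, 30.1, 43.1, then 69.2 | 13.0 |
| First scan at 6 | 6, 19.0, 32.1, 45.1, then 71.2 | 13.0 |

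Every gap between consecutive year-1 scans is below 16 weeks. The PET/CT alternative (3 months, then 3-monthly) also has 13-week gaps.

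**3. First qualifying scan, by when response is first seen.**
- First scan: 20.1-22.1 weeks later (counting from end of radiation) or 26.1 weeks later (counting from first scan).
- Other year-1 scans before the second-to-last: 26.1 weeks later.
- Second-to-last year-1 scan: 39.1 weeks later, because the next gap is 13.0 and the following one is 26.1.
- Last year-1 scan: 26.1 weeks later, which is the next scheduled scan, so nothing is lost.

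**4. Size of the loss.** Loss = 1 − S(first qualifying scan)/S(next scheduled scan), the share of responses still held at the next scan but gone by the qualifying one. Except for the last two year-1 scans, the extra wait is 3 months. With exponential progression at median m, loss = 1 − 2^(−3/m).

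| Assumed median m (months) | Source | Loss |
|---|---|---|
| 6.4 | Section 16, chemotherapy-alone assumption | 27.7% |
| 8.0 | 6.4 × 1.25, the increase to be detected | 22.9% |
| 12 / 18 / 24 | assumed for responders | 15.9% / 10.9% / 8.3% |

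For a response first seen at the second-to-last year-1 scan the extra wait is 6 months: 1 − 2^(−6/6.4) = 47.8%, or 40.5% at 8.0 months.

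**5. Sensitivity.**
- Unscheduled scan at exactly 16 weeks, where the next scheduled scan is 13 weeks away: the extra wait is 3.68 − 3 = 0.68 months, so the loss is 1 − 2^(−0.68/m) = 7.1% (6.4) or 5.7% (8.0).
- Section 16's SD of 3.2 months read as a normal distribution, S(t) = 1 − Φ((t − μ)/3.2), with response at the first scan. That scan falls at day 19 plus 4-6 weeks, or 1.54-2.0 months. For μ = 6.4 and 1.54 months, S(4.54) = 0.719 and S(7.54) = 0.361, a loss of 50%. Over the range the loss is 50-54% for μ = 6.4 and 35-39% for μ = 8.0.

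**The case against.** The mismatch itself is hard to dispute, but several stronger readings are tempting and do not stand.

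- **That about a quarter of responses are lost.** The protocol gives no response duration and no PFS for responders. The 23-28% requires exponential progression, responders progressing at the all-patient rate with the clock restarted at response, and no unscheduled scan. The exponential form does not agree with the protocol's own input, "we will assume a median time to progression of 6.4 months (standard deviation 3.2 months) with chemotherapy alone": an exponential with median 6.4 has SD 6.4/ln 2 = 9.2 months. The 6.4 and 8.0 months are the chemotherapy-alone benchmark and the increase to be detected, not forecasts for responders.
- **That the next scan never qualifies.** This fails for a response first seen at the last year-1 scan, which the next scan, 26 weeks later, can confirm.
- **That a response cannot be confirmed at all.** The rule sets a minimum without an upper limit. Responses that last are confirmed, only later, and an unscheduled scan at 16 weeks is not forbidden. Relying on such scans would, however, leave confirmation to individual discretion.
- **That the rate is biased.** Response rate has no target, null value or comparator here. A longer interval defines a stricter endpoint, and Section 13's caution about telling residual disease from normal tissue could be a reason to want one.

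What remains is that nothing in the protocol says a durable response endpoint was intended, labels it as such, or schedules a scan to suit it.

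**Conclusion.** The point holds as an internal inconsistency on a secondary endpoint. Section 13's 16-week minimum exceeds every gap between consecutive year-1 scans in Section 7.4 and the synopsis schedule table. Apart from responses first seen at the last year-1 scan, confirmation on the calendar waits for the second following scan or later, and the reported rate measures response sustained for roughly 5-6 months without saying so.

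The direction is certain for responses that end between the next scan and the qualifying one; the size is not. It runs from about 6-7% (unscheduled 16-week scan) through 8-16% (responder median 24-12 months) and 23-28% (exponential at 8.0-6.4 months) to 35-54% (normal with SD 3.2). Each figure is conditional on its assumption and none is a document figure. The PFS and OS objectives and the 87% and 70% power statements are unaffected. It is worth correcting because the correction is cheap, not because the trial's main conclusions depend on it.

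**What to change.** Reconcile Section 13 with Section 7.4 and the synopsis schedule table by one sentence in Section 13: a CR or PR is confirmed if the criteria are still met at the next scheduled assessment. This needs no new scans. Show durability through the duration of response that Section 13 already defines, counted from when the criteria are first met.

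If the sponsor did intend a durable response endpoint, keep the 16 weeks, name the endpoint accordingly in Sections 1 and 16, and align the scan calendar with it.

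The cost of the first option is that some shorter responses will count as confirmed; reporting duration of response beside the rate makes this visible.
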